### Randomization and blinding

After informed consent is obtained, block randomization is employed. An independent administrator not involved in this study sets a block length of 4, generating a random sequence using the online Sealed Envelope tool. Participants are randomized in a 1:1 ratio to either the taVNS group or the sham group. During this process, allocation concealment is guaranteed by using sealed envelopes and the anesthesiologist responsible for the surgery has no a priori knowledge of the intervention assignment. The medical team providing care during the perioperative period, outcome assessors, investigators, and patients are also blinded to the group assignment. After the participant enters the operating room, an anesthesia assistant who is not involved in the data collection and outcome assessment opens the envelope in the absence of the anesthesiologist, assigns the patient to either the taVNS or the sham group, sets the vagus nerve electrical stimulation parameters, and places the vagus nerve electrical stimulation device into an opaque black bag. The anesthesiologist then performs anesthesia induction immediately. Due to the anterograde amnesic effect of anesthesia, the patient remains unaware of the intervention postoperatively. To ensure the effectiveness of patient blinding, a random selection of patients is surveyed before unblinding to determine which group they believed they had been assigned to. The proportion is then calculated, and if it is close to 1:1, it indicates successful blinding. Follow-up personnel and ward staff remain unaware of the group assignments. After statistical results are generated, unblinding is performed for all participants.

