### Sample size

The sample size was calculated with the PASS 15.0 software. It is reported the incidence of PONV among Chinese patients undergoing elective gynecological laparoscopic surgery is approximately 40% following dual-agent prophylaxis with dexamethasone and ondansetron [5]. Based on previous studies, we assume that the incidence of PONV in the taVNS group would be reduced to 20%[22,23]. To provide a significance level of 0.05 and a power of 0.8, a sample size of 158 patients will be required. Considering potential protocol deviations and withdrawal of consent, the recruitment target will be increased to 100 patients in each group.

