### Statistical plan

Two members of the research team will perform study consolidation and analysis. All statistical plans will be finalized prior to unblinding. Categorical data will be expressed as frequencies and percentages and continuous variables will be expressed as means and standard deviations for normally distributed variables or otherwise as medians and interquartile range. The Kolmogorov–Smirnov test will be used to detect the normality of distribution. The statistical analysis will be conducted using R software (version 4.3.1 or higher) and SAS software (version 9.4 or higher).

Patient demographic and baseline characteristics will be summarized using descriptive statistics for each group. No hypothesis testing will be performed for between-group comparisons at baseline. The balance between the taVNS and the sham group will be evaluated by calculating standardized mean differences (SMDs), with an SMD > 0.10 indicating substantial imbalance.

The primary endpoint, the incidence of PONV within 24 h postoperatively, will be analyzed in both the intention-to-treat (ITT) population (all randomized patients) and the per-protocol (PP) population (excluding patients with major protocol deviations, such as failure to apply stimulation, incorrect stimulation parameters, or surgical conversion). Between-group comparisons for the primary endpoint will be performed using the Chi-square test or Fisher’s exact test, as appropriate. The treatment effect will be reported as relative risk (RR) with a 95% confidence interval (CI). A multivariable logistic regression model will be fitted to adjust for potential confounding factors (baseline covariates with SMD > 0.10), with results presented as an adjusted odds ratio (OR) with 95% CI. Missing data for the primary endpoint will be handled under the missing-at-random assumption using multiple imputation.

All secondary endpoints will be analyzed in the ITT population only. The severity of postoperative nausea (NRS scores) will be compared between groups using the independent t-test or Mann-Whitney U test, with the effect size reported as the difference in means or medians with 95% CI. The use of rescue antiemetics and patient satisfaction scores will be compared using the Chi-square test (or Fisher’s exact test) and the Mann-Whitney U test, respectively. A Bonferroni correction will be applied for the three secondary endpoint comparisons, setting the significance level at *p* < 0.017 (0.05/3).

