## Discussion

The study employed a randomized, double-blind, and sham-controlled design. This clinical study will group 200 gynecological patients who undergo laparoscopic surgery, and they will respectively receive left auricular vestibular vagus nerve electrical stimulation and sham stimulation. The primary endpoint is whether the incidence of postoperative nausea and vomiting (PONV) can be reduced. The secondary outcomes include determining whether the severity of nausea can be alleviated, reducing the dosage of antiemetic drugs, and improving patients’ satisfaction. The exploratory endpoints mainly include heart rate variability during the operation and the use of opioid drugs within 24 h after the operation. We will complete this trial in accordance with the Consolidated Standards of Reporting Trials guidelines.

PONV is a pivotal factor affecting the quality of postoperative recovery. taVNS represents a promising non-pharmacological intervention in PONV prevention [11,24,25]. The study employed a randomized, double-blind, and sham-controlled design to verify its effectiveness. Such a design minimizes bias and yields high-quality evidence. The intervention is administered intraoperatively, targeting a critical window within the neural pathways central to PONV pathogenesis.

If the study yields positive findings demonstrating a significant reduction in PONV incidence with taVNS, substantial clinical implications will be identified. First, the magnitude of PONV reduction achieved by taVNS should be compared with other established or emerging strategies, such as combined antiemetic regimens. This would establish its role in a multimodal PONV management strategy. Second, observed reductions in nausea severity and rescue antiemetic consumption have direct clinical relevance, as they confer potential advantages regarding patient comfort and alignment with enhanced recovery after surgery (ERAS) pathways. Detailed reporting of intraoperative anesthetic parameters including opioid and propofol doses provides essential context for interpreting PONV outcomes and enables comparison with other studies using comparable protocols.

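### Plain Bonferroni at a fixed p < 0.017 gives away power on the three secondary endpoints; Holm's procedure holds the same 5% at no cost

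*Protocol article*

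**What the plan says.** The Sample size section sets the primary endpoint's error rate and power: "To provide a significance level of 0.05 and a power of 0.8, a sample size of 158 patients will be required". The Statistical plan section then treats the secondary endpoints (nausea severity, rescue antiemetic use, satisfaction) as their own family: "A Bonferroni correction will be applied for the three secondary endpoint comparisons, setting the significance level at" p < 0.017, shown there as 0.05/3. The same threshold applies to all three, whatever the other two show.

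The section does not make these tests depend on the primary result, and it does not claim one joint error rate for primary and secondary endpoints. Exploratory endpoints are left uncorrected, with little weight put on their p-values. In the Discussion, the remark that "observed reductions in nausea severity and rescue antiemetic consumption have direct clinical relevance" stands in a paragraph that opens by supposing a significant fall in PONV incidence.

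**The concern.** Bonferroni compares every p-value with 0.05/3, even after one or two of the hypotheses have been rejected. Holm compares the smallest p-value with 0.05/3, the next with 0.05/2 and the last with 0.05, and stops at the first failure. Both hold the chance of any false claim among the three at 5% or less, under any dependence between the endpoints. The fixed threshold can therefore leave a second or third real effect undeclared with no gain in protection. For example, p-values of 0.010, 0.020 and 0.040 give one significant result under the current rule and three under Holm.

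This matters here because the trial is sized on its primary alone, so the article guarantees no particular power for the secondaries.

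A side question is what happens when the primary fails. The text shown states no testing order, so the primary's 5% and the secondary family's 5% stand next to each other.

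**Working it through.** **The plan's own figures.** 0.05/3 = 0.01667, printed as 0.017, so the threshold reproduces. The primary's size also reproduces. With 40% against 20%, 1:1 allocation, two-sided 0.05, power 0.80 and unpooled variance, (1.960 + 0.842)² × (0.24 + 0.16)/0.20² = 78.5, so 79 per group and 158 in total. Sidedness is not stated; two-sided is assumed because it gives 158.

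**Assumptions not in the article.** Each secondary has 80% power when tested alone at two-sided 0.05, so its test statistic has mean 1.960 + 0.842 = 2.802. All pairs of endpoints share one correlation, varied from 0 to 0.9.

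**Bonferroni, per endpoint.** The critical value at 0.05/3 is 2.394. Power = Φ(2.802 − 2.394) = Φ(0.408) = 0.658, at any correlation.

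**Holm.** Simulated with one million draws of correlated normal statistics. Check by hand at correlation 0:
- A single test falls below 0.05/3 with probability 0.658, below 0.025 with 0.712, and below 0.05 with 0.80. The two bands between these limits have probability 0.054 and 0.088.
- All three below 0.05: 0.80³ = 0.512.
- Subtract the cases with fewer than two below 0.025: 3 × 0.712 × 0.088² + 0.088³ ≈ 0.017.
- Subtract the cases with at least two below 0.025 but none below 0.05/3: 0.054³ + 3 × 0.054² × 0.088 ≈ 0.001.
- Result: 0.494, as simulated. Bonferroni gives 0.658³ = 0.285.

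**Power by correlation.** "Gated" in the table means that Holm is applied only if a primary with 80% power, correlated to the same degree, is significant at 0.05.

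| Correlation | Bonferroni: each / all three | Holm: each / all three | Gated Holm: each / all three |
|---|---|---|---|
| 0 | 66% / 29% | 75% / 49% | 60% / 40% |
| 0.3 | 66% / 36% | 74% / 55% | 63% / 48% |
| 0.5 | 66% / 42% | 73% / 59% | 65% / 54% |
| 0.7 | 66% / 48% | 73% / 63% | 67% / 60% |
| 0.9 | 66% / 56% | 72% / 68% | 70% / 67% |

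The Holm value per endpoint at 0.5 is 73.4% to 73.5% across simulation runs. The chance of at least one significant secondary is the same under Bonferroni and Holm (87% at 0.5), because both start at 0.05/3. With the gate it falls to 74%.

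**Error within the secondary family, no true effects.** Bonferroni and Holm agree, since the first false claim needs a p-value below 0.05/3: 4.9% if independent, less if correlated.

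**Primary and secondaries together, current rule, no true effects.**
- Upper bound: 0.05 + 3 × 0.05/3 = 10.0% (10.1% with 0.017 as printed).
- Independent: 1 − 0.95 × (1 − 0.01667)³ = 9.7% (9.8% with 0.017).
- Correlation 0.3, 0.5, 0.7, 0.9: 9.2%, 8.5%, 7.3%, 5.7%.
- Primary not significant but at least one secondary significant: 4.7% if independent, 3.5% at 0.5, 0.7% at 0.9.

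**The case against.** Bonferroni is valid and controls exactly what the plan says it controls. Lower power on secondary endpoints is not a mistake in a trial sized for its primary. That stands: this is an improvement, not the repair of an invalid test. But the improvement is free. One usual reason to keep Bonferroni is that it has matching simultaneous confidence intervals, and the plan does not use them; it reports ordinary 95% intervals.

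A reader might go further and infer that the trial breaches a 5% error rate, or that it has one definite overall rate above 5%. The article supports neither. It never promises a joint 5% over primary and secondary endpoints, and separate families are common practice. The primary's own 5% is untouched and the secondary family is held at about 5%. Any single overall figure needs a correlation that the article does not give. Severity and rescue use record the same symptoms as the primary, so for them the low-correlation end, where the excess is largest, is the less plausible one.

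A reader might also infer that the plan endorses secondary claims after a failed primary. It does not say so; it is silent on order, and a testing order may stand in the full protocol or analysis plan, which is not shown. The Discussion paragraph describes implications of a positive trial and is not a testing rule.

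Finally, the power gain belongs to Holm without a gate. It cannot be used to argue for Holm and a gate together: at correlation 0.5, gated Holm gives about 65% per endpoint against 66% now.

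**Conclusion.** The point holds for the choice of procedure within the secondary family. Under the stated assumptions, Holm adds about 6 to 9 percentage points of power per endpoint and about 13 to 21 points for all three, over correlations from 0.9 to 0, at the same 5% family-wise error. It does not change the chance of at least one significant secondary. The size of the gain rests on the assumed 80% power and common correlation; that Holm never rejects less than Bonferroni at 0.05/3 rests on neither. The one exception to the printed rule is trivial: a smallest p-value between 0.01667 and 0.017 passes only because of the rounding, which lets the family's error reach 5.1% at most.

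The missing condition on the primary is a design choice to make openly. Its size is bounded at about 10% for all four claims together, with a range of about 6% to 10% over assumed correlations from 0.9 to 0. A gate would bring that to 5% but costs secondary power. At correlations up to 0.5 it takes per-endpoint power to the level of the current rule or below; at 0.9 about 4 of the 6 points gained remain.

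**What to change.** In the Statistical plan section, replace the fixed p < 0.017 with Holm's procedure at an overall two-sided 0.05 for the three secondary endpoints: smallest p-value against 0.05/3, next against 0.05/2, last against 0.05, stopping at the first that fails. Each endpoint must supply one p-value, as the plan's count of three implies. The cost is one sentence. Data, sample size and trial conduct do not change. Recruitment was still under way when the article was revised, and the plan is to be finalised before unblinding, so the change can still be made.

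Optionally, state the status of the secondaries in one further sentence:
- test them only if the ITT primary analysis is significant at 0.05, and otherwise report estimates with intervals; or
- keep them ungated and label them supportive.

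The first holds all four claims at 5%, but allows no formal secondary claim if the primary fails and, at correlation 0.5, cancels the per-endpoint gain from Holm. The second keeps the gain and leaves the joint rate at up to about 10%.

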## Discussion

The study employed a randomized, double-blind, and sham-controlled design. This clinical study will group 200 gynecological patients who undergo laparoscopic surgery, and they will respectively receive left auricular vestibular vagus nerve electrical stimulation and sham stimulation. The primary endpoint is whether the incidence of postoperative nausea and vomiting (PONV) can be reduced. The secondary outcomes include determining whether the severity of nausea can be alleviated, reducing the dosage of antiemetic drugs, and improving patients’ satisfaction. The exploratory endpoints mainly include heart rate variability during the operation and the use of opioid drugs within 24 h after the operation. We will complete this trial in accordance with the Consolidated Standards of Reporting Trials guidelines.

PONV is a pivotal factor affecting the quality of postoperative recovery. taVNS represents a promising non-pharmacological intervention in PONV prevention [11,24,25]. The study employed a randomized, double-blind, and sham-controlled design to verify its effectiveness. Such a design minimizes bias and yields high-quality evidence. The intervention is administered intraoperatively, targeting a critical window within the neural pathways central to PONV pathogenesis.

If the study yields positive findings demonstrating a significant reduction in PONV incidence with taVNS, substantial clinical implications will be identified. First, the magnitude of PONV reduction achieved by taVNS should be compared with other established or emerging strategies, such as combined antiemetic regimens. This would establish its role in a multimodal PONV management strategy. Second, observed reductions in nausea severity and rescue antiemetic consumption have direct clinical relevance, as they confer potential advantages regarding patient comfort and alignment with enhanced recovery after surgery (ERAS) pathways. Detailed reporting of intraoperative anesthetic parameters including opioid and propofol doses provides essential context for interpreting PONV outcomes and enables comparison with other studies using comparable protocols.

The individualized current titration protocol based on the comfort sensory threshold before anesthesia induction is essential to ensure patients’ comfort and achieve consistent neurophysiological effects among patients [26]. Compared to multi-session protocols such as pre-, intra-, and postoperative protocols, the single intraoperative stimulation regimen presents distinct advantages and limitations concerning efficacy and clinical feasibility, meriting further discussion. Intraoperative stimulation targets the key window of PONV pathogenesis under anesthesia. It allows precise control and standardized delivery, unlike patient-dependent pre/post-op sessions. This pragmatic approach simplifies clinical implementation and trial design. The intraoperative timing of stimulation, while pragmatic, presents inherent limitations. First, its restricted window may not address preoperative anxiety or later-onset PONV occurring beyond 24 h. Second, the depth of general anesthesia could potentially attenuate the targeted neural response, possibly diminishing the intervention’s effect. Finally, this design does not allow us to explore whether a preemptive or multi-session strategy might yield superior outcomes. Moreover, maintaining successful blinding is paramount to minimizing bias in subjective outcomes, such as nausea scores and patient satisfaction; consequently, the blinding assessment employed in this study design will provide valuable insights for future.

Previous studies have shown that only mild and transient adverse events, such as erythema at the electrode site have been reported with taVNS [27]. In contrast, common antiemetic drugs are associated with side effects such as metoclopramide-induced oculogyric crisis [28], as well as potential sedation, headache, and QT interval prolongation linked to 5-HT3 receptor antagonists [29–31]. This highlights the potential advantage of taVNS in reducing polypharmacy and related drug side-effects. At present, no potential risks associated with left ear vagus nerve stimulation such as bradycardia and hypotension have been observed, likely due to the use of low-intensity transcutaneous auricular stimulation rather than invasive cervical vagus nerve stimulation. Additionally, theoretically, the right vagus nerve mainly controls the sinoatrial node [32]. Therefore, the possibility of experiencing bradycardia and hypotension due to stimulation of the right vagus nerve is greater. Furthermore, we collect patient-reported outcomes, including postoperative satisfaction. Exploratory analyses also detect the influence on opioid consumption of taVNS. These explorations require cautious interpretation, provide a more comprehensive assessment of the intervention’s utility and its impact from the patient’s perspective. Finally, preliminary subgroup analyses exploring whether the treatment effect is consistent across different ages or Apfel risk categories will need confirmation in future, larger trials.

This study is subject to several limitations. The findings of the single-center study require verification through multi-center studies with larger sample sizes. The relatively short follow-up period (24 h) may not fully capture late-onset PONV or potential sustained effects of taVNS. A single intraoperative stimulation may be insufficient, especially during prolonged surgeries, increasing the risk of a negative result. We plan subgroup analyses based on surgical duration. The results of this subgroup analysis may inform the design of future trials investigating optimized stimulation protocols. Despite the application of blinding, the distinct sensory perception induced by taVNS may compromise the blind in some patients or assessors. To verify the integrity of the blinding procedure, we will assess the final distribution of participants across study groups. A ratio close to 1:1 would provide indirect evidence of the validity of the outcome assessment under blinded conditions.

In conclusion, this study will provide key evidence on the efficacy and safety of intraoperative taVNS as a non-pharmacological and minimally invasive strategy for preventing PONV after gynecologic laparoscopic surgery. Positive results could support the application of taVNS in PONV management. It offers a novel, well-tolerated treatment option for patients. Furthermore, these results would establish a foundation for future research aimed at elucidating its mechanisms and evaluating its utility in diverse clinical scenarios.

## Data Availability

The full protocol, participant-level dataset, statistical plan, and informed consent materials can be available *via* contacting the corresponding author after the formal publication of this trial.
